### Sample Size Determination

#### Overview

We assume a small to medium effect size (Cohen *d*=0.33) of the current intervention according to a meta-analysis of SSIs addressing youth psychiatric problems [13], a power of 0.80 and an α of .05. A sample size of 438 (146 per arm) is required to detect statistical significance. With reference to the approximately 20% attrition rate of our previous studies in the school setting, 549 pairs of parent-student participants will be recruited at the baseline (183 per arm). Our existing research suggests that this is feasible within the timeframe.

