### Data Analysis

An intention-to-treat approach will be adopted. A 2-level analysis will be used to account for the cluster randomization [52]. To examine the effects of the interventions, multilevel regression will be used to test the group effect, time effect, and interaction effect on outcome measures. Additionally, we will calculate effect sizes using estimated marginal means; these effect sizes compare mean change scores (Cohen *d*), reflecting the standardized levels of change in each outcome from baseline to 2 follow-ups for youths receiving the mindset versus active control interventions. A 95% CI will be provided for each effect size. SPSS (version 26; IBM Corp) will be used for all statistical analysis.

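### The planned contrast is, on the natural reading, an unadjusted difference in change; adjusting for the baseline score would save roughly 10–30% of its variance at no cost

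*Protocol article*

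**What the plan says.** All references are to the protocol article.

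- **Model (Data Analysis).** "multilevel regression will be used to test the group effect, time effect, and interaction effect on outcome measures". A two-level analysis is to account for the cluster randomisation.
- **Effect size (Data Analysis).** In addition, Cohen d values are derived from estimated marginal means: "these effect sizes compare mean change scores", "reflecting the standardized levels of change in each outcome from baseline to 2 follow-ups". Each gets a 95% CI. The SD that serves as divisor is not named.
- **Occasions (Research Design).** Students in all three groups are assessed at baseline, 2 weeks and 3 months. Under Expected Findings, the 3-month assessment is treated as primary.
- **Covariates.** Gender, age, grade and socioeconomic status are collected to look at differences between the groups. The baseline value of the outcome is not listed.
- **Sample size (Overview).** The planning value is a "small to medium effect size (Cohen *d*=0.33"), with "a power of 0.80 and an α of .05". "A sample size of 438 (146 per arm) is required to detect statistical significance".

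No correlation between baseline and follow-up and no intraclass correlation is given.

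**The concern.** If baseline is one of the modelled occasions and each arm has its own mean there, the group-by-time contrast with complete data is the difference between arms in mean change. Randomisation makes the true baseline means equal, so that model estimates something already known and pays for it in variance. Subtracting the whole baseline score also over-corrects a chance imbalance. With equal variances, given a baseline difference D between two arms, the expected difference in change is the true effect minus (1−ρ)D. Chance differences in class make-up are likely when only about eight classes go to each arm.

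Precision matters here. The stated sample size is what an individually randomised two-group comparison needs, while classes are randomised. The hypotheses also ask PC-SMILE to beat C-SMILE, not only the waitlist.

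**Working it through.** **1. The plan's own figure.** Inputs from the Overview of the sample size section: d = 0.33, power 0.80, α = 0.05 (two-sided, since one-sided gives 114 per arm and does not match).

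n per arm = 2(1.96 + 0.8416)² / 0.33² = 144.2, so 145. The t-based solution is 145.1, so 146 per arm and 438 in all. Allowing for 20% attrition, 146 / 0.8 = 182.5, so 183 per arm and 549 in all. The stated figures reproduce. They use neither a baseline correlation nor a clustering allowance.

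**2. Variance per student, in units of the score variance (equal variance at both occasions).**

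- Difference in change: 2(1−ρ)
- Baseline-adjusted: 1−ρ²
- Share saved: 1 − (1−ρ²)/[2(1−ρ)] = 1 − (1+ρ)/2 = (1−ρ)/2

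ρ is assumed throughout. The n and power columns take d = 0.33 in score SDs, use a normal approximation and ignore clustering.

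| ρ (assumed) | change | adjusted | saved | n per arm, change / adjusted | power at 146 per arm, change / adjusted |
|---|---|---|---|---|---|
| 0.4 | 1.20 | 0.84 | 30% | 173 / 122 | 73% / 87% |
| 0.5 | 1.00 | 0.75 | 25% | 145 / 109 | 80% / 90% |
| 0.6 | 0.80 | 0.64 | 20% | 116 / 93 | 88% / 94% |
| 0.7 | 0.60 | 0.51 | 15% | 87 / 74 | 95% / 98% |
| 0.8 | 0.40 | 0.36 | 10% | 58 / 52 | 99% / 100% (0.994 / 0.997) |

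A simulation with 146 per arm and 4,000 runs gave savings of 28%, 26%, 20%, 16% and 10% for these five values, in line with the formula. At ρ = 0.9 the saving is 5%. Below ρ = 0.5 the change score is less precise than the follow-up score alone, because 2(1−ρ) exceeds 1.

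**3. Class randomisation.** The relevant correlation is then that of class means. Take 8 classes per arm (8 schools with 3 classes each) and m = 146 / 8 = 18.25 evaluable students per class. With ICC as the class share of variance and ρc as the class-level correlation:

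- variance of a class mean: v = ICC + (1−ICC)/m
- covariance of the two occasions: c = ρc·ICC + ρ(1−ICC)/m
- R = c/v, and the share saved is (1−R)/2

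Example with ICC = 0.02, ρ = 0.5, ρc = 0.8:

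- v = 0.02 + 0.98/18.25 = 0.0737
- c = 0.016 + 0.5 × 0.0537 = 0.0429
- R = 0.581, so 21% is saved

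Over assumed ICC 0.01–0.05, ρ 0.5–0.7 and ρc from ρ up to 0.9, the saving runs from 25% (ρc = ρ = 0.5) down to 10% (ICC 0.05, ρ 0.7, ρc 0.9).

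**4. Power under clustering, as illustration only.** Two arms of 8 classes of 18 students, d = 0.33, class-level t-tests, 4,000 runs. The class and class-by-time variance shares are assumed.

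| ρ | class / class-by-time share | power, change | power, adjusted | variance saved |
|---|---|---|---|---|
| 0.5 | 0.02 / 0.01 | 0.61 | 0.73 | 20% |
| 0.6 | 0.01 / 0.01 | 0.69 | 0.78 | 22% |
| 0.7 | 0.02 / 0.01 | 0.77 | 0.83 | 17% |

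With a class share of 0.04 the gain is smaller: 0.62 to 0.68 at ρ = 0.5, and 0.77 to 0.81 at ρ = 0.7.

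**The case against.** **The model is inferred.** The Data Analysis section does not say that baseline is a modelled occasion or that arm means are free there. A model of the two follow-ups with a baseline covariate also has group, time and interaction effects. The sentence on change scores concerns an additional effect size, and regressing change on arm and baseline gives the same arm effect as regressing the follow-up score on them. This stands as a limit on certainty. But a time effect tested alongside change from baseline, with no baseline score among the covariates, points to the unadjusted contrast as the natural reading.

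**It is a valid analysis.** A group-by-time mixed model is unbiased under randomisation, and the stated sample size does not depend on baseline adjustment. Both are true. The point is efficiency only.

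**Detail for the analysis plan.** An article may leave the parameterisation to a fuller document. However, this article does name its model and the quantity it reports, and a better choice needs no new data.

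**The power shortfall is mostly clustering.** Without clustering, change scores at ρ of 0.5 or more give at least 80% power at 146 per arm. This stands: the low powers in the clustered illustration come chiefly from the assumed class variance, which is a separate matter.

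**Eight classes per arm is not fixed.** Class selection is repeated until a school yields 70 pairs, so there may be more classes. This stands too.

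**Conclusion.** The concern holds as an avoidable loss of precision. On the natural reading, the contrast carries more variance than one that uses the baseline score the trial measures anyway. The saving from adjustment is (1−ρ)/2: about 10–30% for an assumed ρ of 0.8 to 0.4, and about 10–25% for class means under the assumed ICCs and correlations. In large samples its direction is the same for every ρ below 1. Its size cannot be fixed from the article, and any gain in power is conditional on the assumed ρ and clustering.

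Three stronger readings are tempting and not supported:

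- **A definite loss of 15–25%.** That range is exactly ρ = 0.7 to 0.5 in the student-level formula, and the article gives no ρ.
- **A biased effect.** Over-correction of a chance imbalance is conditional on the imbalance and averages out over randomisations.
- **A reported d inflated relative to the planning d.** This would need division by the SD of change, and the article names no divisor. What can be said is that the scale of d should be stated, the more so because the Results section says an effect size from the first school may lead to a change in sample size.

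**What to change.** In the Data Analysis section, keep the multilevel model and its allowance for classes, and state one of two forms:

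- model the 2-week and 3-month scores with arm, visit and arm by visit, with the baseline value of the same score as covariate; or
- keep all three occasions and constrain the arms to a common baseline mean. This form also keeps students who have a follow-up score but no baseline score, which suits the intention-to-treat aim.

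Report the adjusted 3-month difference for each pair of arms with its 95% CI. Define d as that difference divided by the pooled baseline SD, and use the same definition for any effect size taken from the first school.

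The cost is wording only. The baseline assessment is already scheduled in every arm. According to the Results section, only the first school (75 students) had joined, with data collection due to run to April 2025, so the change could be made before most of the data exist.

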### Ethical Considerations

Research ethical approval has been obtained from the Hong Kong Polytechnic University institutional review board for Ethical Review (HSEARS20211009001). Participation will be voluntary. Informed written consent will be obtained from participating parents and students. Participants will be reminded that they have the right to terminate the intervention or abstain from responding to any question on the questionnaire without providing a reason, and they will be assured of confidentiality. Additional information for referral services will be provided to participants with clinical-level mental health needs. All identifiable information will be removed, and codes will replace names to ensure privacy. All personally identifiable data will be stored on a secure server and destroyed 3 years after the study ends. Participants’ data will not be identifiable in any publication or reporting. Each participating family in the study will receive a HK $100 (≈US $12) supermarket voucher after the intervention and another one after the 3-month follow-up, making the total compensation for each family HK $200 (≈US $40).

## Results

We have started school invitation and participation recruitment in September 2023. The first school joined the study in May 2024. 75 students from 3 classes were randomly assigned into 3 groups. Students completed baseline surveys and intervention at school, while parents completed baseline assessment and intervention at home. Those have done the baseline receive reminders to complete the baseline assessment or intervention within 1 week after the baseline. Follow-up assessments will be finished by September. Meanwhile, we will send invitations to other schools until we have a sufficient sample size. The effect size will be calculated based on the data of the first school, and the sample size may be adjusted. We will conduct data collection from September 2024 to April 2025 and complete all follow-up surveys by April 2025.

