**Methods:**

A total of 549 parent-child dyads will be recruited from 8 secondary schools and randomly assigned to either the PC-SMILE intervention group, the C-SMILE intervention group, or the no-intervention waitlist control group. The 45-minute interventions include parent-version and child-version. Both parents and students in the PC-SMILE group receive the intervention. Students in C-SMILE group receive intervention and their parents will receive intervention after all follow-up ends. Students in 3 groups will be assessed at 3 time points, baseline before intervention, 2 weeks post intervention, and 3 months post intervention, and parents will be assessed in baseline and 3-month follow-up. The intention-to-treat principle and linear-regression-based maximum likelihood multilevel models will be used for data analysis.

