Students and parents will complete all study procedures via personal internet-equipped devices. Parent-student pairs will be assigned to the same condition (the PC-SMILE or C-SMILE or waitlist). They will receive the link of research material and complete Qualtrics-based baseline survey, intervention, and follow-up surveys independently. For student participants, the interventions will be conducted in school classrooms or activity rooms that offer sufficient computers or tablets, and headphones. All intervention activities will be self-administered by youths and delivered in a web-based format. The research team and trained research assistants will remain in the intervention rooms to provide help if needed. Parent participants will receive a study link with the baseline Qualtrics survey and the intervention. The interventions for parents and students are different in terms of narrative and content. Between the 2-week posttest and the 3-month follow-up survey, a total of 5 weekly booster messages with core intervention content will be sent to the intervention groups every 2 weeks. After completion of the 3-month follow-up, parents in the C-SMILE or the control group who do not initially receive the intervention will be granted the intervention access.

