#### C-SMILE Group

In the C-SMILE group, only students receive the child-version intervention, but their parents do not receive parent-version intervention until the 3-month follow-up is finished. Parents are invited to do the preintervention survey and the 3-month follow-up survey.

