### Primary Outcome

Children’s depression and anxiety symptoms will be measured using the validated 25-item Revised Children’s Anxiety and Depression Scale for both children and parents [44,45]. Sample items measuring anxiety and depression include “I/My child worry when I/My child think I/My child have done poorly at something” and “‘I/My child feel sad or empty.” The frequency of each item is rated on a 4-point Likert scale with reference to the past 2 weeks (0=never to 3=always). The child survey has an overall score, total anxiety score from the anxiety subscale (Cronbach α=0.94), and total depression score from the depression subscale (Cronbach α=0.79) [44].

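### Nothing in the described procedure makes parents complete their baseline before the child's session, so parent-reported baselines in the two treated arms may be post-intervention

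*Protocol article*

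**What the plan says.** Under Participants and the Randomized Control Process, students and parents "complete Qualtrics-based baseline survey, intervention, and follow-up surveys independently". On the parent link the same section says "Parent participants will receive a study link with the baseline Qualtrics survey and the intervention".

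Results reports, for the first school, "Students completed baseline surveys and intervention at school, while parents completed baseline assessment and intervention at home". The next sentence is "Those have done the baseline receive reminders to complete the baseline assessment or intervention within 1 week after the baseline".

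The intended timing appears in two places. The Abstract (Methods) lists the student assessments and then the parent ones: "baseline before intervention, 2 weeks post intervention, and 3 months post intervention, and parents will be assessed in baseline and 3-month follow-up". The C-SMILE Group section says "Parents are invited to do the preintervention survey and the 3-month follow-up survey".

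Primary Outcome names the "validated 25-item Revised Children’s Anxiety and Depression Scale for both children and parents", with items "rated on a 4-point Likert scale with reference to the past 2 weeks". Secondary Outcomes adds a parent version of the parent-child relationship items. Data Analysis tests group, time and their interaction, and expresses effect sizes as differences in change from baseline.

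**The concern.** A baseline is useful here only if it precedes any exposure that could move the rating. The parent rates the child, so the relevant exposure is the child's session as well as the parent's own module. The child's session is fixed at school and the parent's survey floats at home. A parent who answers late in PC-SMILE or C-SMILE then rates a child who has already been treated. A parent who answers equally late in the waitlist arm rates an untreated child, because that arm gets its intervention only after the 3-month survey.

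Parents have two assessments, so each parent-reported effect is the change from this one baseline to 3 months. Early benefit already present in treated-arm baselines, and absent from waitlist baselines, is subtracted from the effect. The outcomes at stake are the parent-reported symptom scale and the parent-reported relationship items, mainly in the comparisons with waitlist. Between PC-SMILE and C-SMILE the distortion would largely cancel if late answering were equally common in both arms.

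**Working it through.** **1. What the reminder sentence permits.** Taken literally, people who have done the baseline are reminded to do it. It names neither parents nor students, nor whose baseline starts the week.

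- *Reading A: the baseline is the class's school session and the people reminded are parents at home.* The sentence then makes sense, and a parent baseline can fall up to 7 days after the session.
- *Reading B: the baseline is the participant's own.* The week then covers finishing the survey or doing the module. The date of the parent baseline relative to the child's session is not stated at all.

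A fits better, since it follows directly on the sentence that puts students at school and parents at home. Under neither reading does any text shown place the parent survey before the child's session. The preintervention label is therefore not secured.

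**2. Share of the recall window after the session.** Inputs: recall of 2 weeks = 14 days (Primary Outcome) and a reminder window of 7 days (Results). This takes the child's baseline and intervention to fall in one school visit, which the text suggests but does not state.

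Share = day of completion / 14.

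- Day 7: 7/14 = 50%.
- Evenly spread over days 0 to 7: mean 3.5/14 = 25%.

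No recall period is given for the relationship items, so this step applies to the symptom scale only.

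**3. The plan's own sample size, as a reference point.** Inputs (Sample Size Determination): d = 0.33, power 0.80, α = .05, taken as two-sided.

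- Normal approximation: 2 × (1.960 + 0.842)² / 0.33² = 144.2, so 145 per arm.
- The t-test solution is 145.1, so 146 per arm, and 3 × 146 = 438.
- Attrition of 20%: 146/0.80 = 182.5, so 183 per arm, and 3 × 183 = 549.

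The stated figures reproduce. Power at 146 per arm is 0.80.

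**4. Illustration of dilution.** Let f be the share of treated-arm parents with a late baseline, and g the share of the 3-month effect already in those ratings. Then d observed = 0.33 × (1 − f × g). The documents give neither f nor g, so both are assumptions. Power is for two arms of 146 and ignores clustering, as the plan's calculation appears to.

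| f | g | d observed | Power |
|---|---|---|---|
| 0.10 | 0.25 | 0.322 | 0.79 |
| 0.25 | 0.25 | 0.309 | 0.75 |
| 0.25 | 0.50 | 0.289 | 0.69 |
| 0.50 | 0.25 | 0.289 | 0.69 |
| 0.50 | 0.50 | 0.247 | 0.56 |
| 0.50 | 1.00 | 0.165 | 0.29 |

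If ratings move in proportion to the share in step 2, g averages 0.25 for late answers spread evenly over the week. The loss is then 0.25 × f: about 6% at f = 0.25 and 12.5% at f = 0.50. Values of g above 0.50 need one of three things: ratings driven by the most recent days, answers after day 7, or an early effect larger than the one at 3 months. The protocol itself allows that effects may wane (PC-SMILE Intervention).

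**The case against.** The strongest reply is that one garbled sentence cannot carry a finding. It does not name parents, it describes the first school and is not put as a rule for all schools, and no late parent baseline is reported. The article is condensed, and its assessment table is in Multimedia Appendix 1, which is not shown. All of this stands. It limits the point to what the procedure permits, and does not show that it happened. The procedure is still described in the article and does not secure the label that the article uses.

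A reader might go further in four ways that the documents do not support.

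- *The primary result is contaminated.* The Hypotheses place the primary outcome in student participants, and the Abstract puts the students' own baseline before intervention.
- *The Abstract contradicts the procedure.* Its wording about baseline preceding intervention is attached to students. The conflict is with the C-SMILE Group section only.
- *Late completion of the parent module undermines PC-SMILE versus C-SMILE at 2 weeks.* A module done late would leave less time before the child's 2-week score, but which session starts that interval is not stated, and Expected Findings makes 3 months primary.
- *Parents learn their arm from the link before rating.* The text says that survey and module share a link. It does not say that the link reveals the arm before the survey is complete.

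Data Analysis also words its change-score effect sizes for youths with two follow-ups, a schedule that parents do not have. That parent-reported outcomes are analysed as change from baseline is therefore an assumption, though a natural one with two assessments. For parents' own hopelessness and well-being, no route is given by which the child's session would shift them within days, so they are left out of the claim.

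**Conclusion.** The point holds as a weakness in procedure. As described, parent baselines in PC-SMILE and C-SMILE may follow the child's intervention, while those in the waitlist arm cannot. Change-based effects on the parent-reported symptom scale and the parent-reported relationship items may be biased toward zero. That direction assumes an early effect with the same sign as the 3-month effect.

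The size cannot be determined from the documents. On the symptom scale, at most half the recall window of a baseline completed within the week would be post-session. With 25% late and half the effect already present, d = 0.33 would appear as 0.29. With 10% late and a quarter present, it would appear as 0.32, which is negligible. The child-reported primary comparison at 3 months is unaffected.

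**What to change.** From the next school on:

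1. Send the parent baseline survey as its own link. Close it before the student session, by the same calendar rule in all three arms, and release the module link afterwards.
2. Rewrite the reminder sentence in Results so that it says who is reminded, to do what, and by when relative to the school session.

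For the first school (75 students in 3 classes), use the Qualtrics time stamps for a sensitivity analysis that excludes parent baselines completed after the class's school baseline session. That session exists in every arm, so one rule applies to all three. Dropping late baselines in the treated arms only would create missingness that differs by arm.

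The cost is one link split in two, a few days' lead time per school, and possibly a few missing parent baselines. The likelihood-based multilevel model named in the Abstract can keep such parents through their 3-month record. Only one of the 8 planned schools is reported to have joined, so most of the sample can still be collected under the corrected procedure.
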